### Power analysis and sample size

We have calculated the sample size based on the primary outcome as follows: (1) the number of actual pairwise tests to be made for the efficacy of the primary outcome and (2) the two-level modelling approach in the final data analysis, in which the type I error has been adjusted. The statistical efficiency will be ensured using the multivariate analysis of variance (MANOVA) method for multiple group comparison. First, given that video gaming is a fairly novel strategy, we will base the sample size calculation (a priori) [32] on a cognitive-efficacy meta-analysis for patients with schizophrenia [33] showing an overall effect size (ES, Cohen’s *d*) of 0.58 on verbal working memory (a primary outcome). Based on our hypothesis, the primary endpoints will be the effects on verbal working memory after 3 and 6 months of cognitive training group (CogniFit), compared with the other two groups: cognitive training vs. entertainment gaming, cognitive training vs. non-gaming control group, and entertainment gaming vs. non-gaming control group. Four pairwise interactions between the contrast of the two comparisons and the two time points will be tested. For multiple comparison tests of four, for a type I error level of 5% (two-sided), an adjusted significant level should be α/2 = (1- (1–0.05)4) /2 = 0.01274 /2 = 0.0064, and the corresponding z score for a one-tailed test should be 2.49. Given the effect size 0.58, assuming equal sample size of the three groups, with a statistical power of 0.8 and α= 0.01274*,* we will require at least 198 subjects (66 per group at follow-up phase) by applying the equation, 2(Z1-β + Z1-α/2)2 / ES2. According to a meta-analysis [33], the total sample size in previous cognitive training studies was around 50 (range 10–138).

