### Data collection and follow-up

To avoid burdening the patients, data will be collected in separate phases (see Table 1):
A preparatory data collection (estimated 45 min) will be collected only once, at the beginning of the study. It aims to collate the background information of the participants to determine their capacity for informed consent and any other potential factors that might restrict participation in the intervention (background information, IQ, medication dosage [based on medical records], MMSE, CDS-C, SAS, BARS, AIMS).2)For the primary (verbal working memory) and secondary outcomes (estimated 75 min) (cognitive and social functioning, experience of pleasure, self-efficacy, negative symptoms), the data will be collected at three points in time: at baseline, after the intervention (3-month follow up) and at a six-month follow-up (6 months after baseline).3)The EEG measures taken during the working memory test will be collected at baseline and 3 months after baseline only (EEG 1 h; rsfMRI and structural MRI, 45 min).

**Table 1 Tab1:** Instruments and study stages

TIME POINTS Instruments	Eligibility screening	Preparatory data	Baseline	Allocation	Intervention	3 month follow-up	6 month follow-up
Inclusion/exclusion criteria	**X**						
Background information		**X**					
IQ (from medical records if available)		**X**					
Current medication dosage		**X**					
Computer use		**X**					
MMSE		**X**					
Calgary Depression Scale for Schizophrenia, CDS-C		**X**					
Simpson-Angus Rating Scale, SAS		**X**					
Barnes Akathisia Rating Scale, BARS		**X**					
Abnormal Movement Involuntary Scale, AIMS		**X**					

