In the main analysis, we will estimate and test efficacy of interventions on the primary and secondary outcomes. Based on the intention-to-treat principle, we will first assess intervention effects on the primary outcome, verbal working memory, by means of multilevel modelling analysis. A two-level model can be built with repeated time points at level 1, and patients at level 2. Two indicator variables, G2 and G3, will be included in the fixed part of the model to estimate and test mean differences between the cognitive training group with computerised exercises (G1) and the entertainment gaming group (G2), as well as between G1 and the non-gaming control group (G3). The baseline difference between G2 and G3 can be tested using a Ward test, based on the regression coefficient estimates of the two indicators. For changes in the outcome over time, two more indicators, variables T2 and T3, in contrast to the baseline time point, T1, will be included in the fixed part of the model to estimate changes from baseline to 3 months, and from baseline to 6 months. To assess the effects of interventions over time, interaction terms between the treatment group indicators, G2 and G3, and time indicators, T2 and T3, will be included in the fixed part of the model. The significantly different demographics between groups identified in the first step of the analysis and other possible confounders will be adjusted by including them in the main effect model. The within-patient random effects of the outcome measurements will naturally be taken into account by the level two variance in the model. A pairwise comparison and other hypotheses on the intervention effects can be tested using a generalised Ward test with an adequate degree of freedom from the modelling analysis. This analysis approach has two main advantages: a statistically highly efficiency and taking missing data into account. The effects of interventions on other secondary outcome measures, normally distributed and measured at three time points, such as patients’ cognitive and social functioning, experience of pleasure, and self-efficacy, will be analysed using the same model, but a separate model for each outcome. A multilevel logistic model will be used for outcomes in binary form, and multilevel multinomial models will be used for ordinal or nominal outcomes. For outcomes measured at two time points only, such as neurocognitive outcomes, the model will have only one time indicator with two interaction terms to test the efficacy of cognitive training with computerised exercises three months into the trial.

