
SPSS (the Statistical Package for the Social Sciences) Missing Values will be used to identify the amount and pattern of missing data. If missing values are few and randomly allocated, the last observation carried forward (LOCF) will be used to replace the missing data. If missing values are not randomly distributed, multiple imputation approaches will be used. A sensitivity analysis will be performed by comparing results from analysis datasets without missing data imputation and with imputation.

In all tests, significant differences between groups will be detected with a 95% confidence level, and *P* values of < 0.05 will be considered significant. Statistical analyses will be carried out with SAS System for Windows, version 9.4 (SAS Institute Inc.) or R statistical software (R Core Team, 2016).

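### The plan fills outcomes that are few and randomly missing by LOCF, which pulls the primary contrast toward zero in the one case where its own mixed model needs no imputation

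*Protocol article*

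**What the plan says.** All the relevant text is in the protocol article under Data analysis, Cognitive and clinical outcomes.

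- **Main model.** "A two-level model can be built with repeated time points at level 1, and patients at level 2". The intervention effect is read from the interactions of the two group indicators with the two follow-up indicators. The primary contrast is therefore a difference in change from baseline, at 3 and at 6 months.
- **What the model is said to do about missing data.** "This analysis approach has two main advantages: a statistically highly efficiency and taking missing data into account".
- **Missing-data rule, benign case.** "If missing values are few and randomly allocated, the last observation carried forward (LOCF) will be used to replace the missing data".
- **Missing-data rule, other case.** "If missing values are not randomly distributed, multiple imputation approaches will be used".
- **Sensitivity analysis.** "A sensitivity analysis will be performed by comparing results from analysis datasets without missing data imputation and with imputation".

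The section puts no figure on *few* and does not say outright which dataset, filled or unfilled, carries the primary result. Power analysis and sample size plans for 16% dropout during the intervention period.

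**The concern.** The two statements work against each other. A likelihood-based mixed model uses every observed visit and gives valid estimates when data are missing at random and the model is correctly specified. That is the advantage the plan claims for it. Once LOCF has filled the empty cells, the model no longer sees any missing data and the advantage is gone. The plan therefore applies a single-value fill in exactly the situation where nothing needs to be filled.

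The fill also bears directly on the primary contrast. The Letter-Number task is measured at baseline, 3 months and 6 months. A patient who leaves before 3 months has only the baseline score to carry forward, so the change is set to exactly zero and then analysed as if it had been measured. At stake are the size of the estimated effect, part of the power that the dropout allowance was meant to protect, and a standard error that is somewhat too small.

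**Working it through.** **Inputs from the protocol article (Power analysis and sample size).** Effect size 0.58; adjusted two-sided alpha 0.01274, z = 2.49; power 0.80; 16% dropout; 66 per group at follow-up and 79 per group randomised.

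**Step 1: reproduce the plan's own figure.** n = 2(0.8416 + 2.49)² / 0.58² = 2 × 11.10 / 0.3364 = 65.99, i.e. 66 per group. (The unrounded z of 2.4909 gives 66.03.) Allowing for dropout, 66 / 0.84 = 78.6, i.e. 79 per group and 237 in all. The plan's figures reproduce.

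**Step 2: expected contrast under LOCF.** Let a proportion d of each arm be lost at random before 3 months. Let g be the mean change common to both arms and δ the added effect of cognitive training. Lost patients contribute zero change, so the expected mean changes are (1 − d)(g + δ) and (1 − d)g. Their difference is (1 − d)δ. The common gain cancels, and no correlation has to be assumed. Because these patients have baseline carried to both follow-up visits, the same factor applies at 6 months.

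**Step 3: approximate power.** Using the plan's normal approximation with unit SD, power = Φ(contrast × √(n/2) − 2.491). Under LOCF, n = 79 with contrast 0.58(1 − d). On observed data, n = 79(1 − d) with contrast 0.58. For example, at 16%: LOCF gives 0.487 × √39.5 − 2.491 = 0.57, so 0.716; observed data give 0.58 × √33.18 − 2.491 = 0.85, so 0.802.

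| Missing from 3 months on | LOCF contrast (true 0.58) | Power, LOCF | Power, observed data |
|---|---|---|---|
| 3% | 0.563 | 0.852 | 0.864 |
| 5% | 0.551 | 0.834 | 0.856 |
| 10% | 0.522 | 0.785 | 0.833 |
| 16% | 0.487 | 0.716 | 0.802 |

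**Step 4: simulation checks (assumptions not in the documents).**

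- The planned two-level model was fitted to simulated data with 79 per arm, two arms, correlation 0.6, common gain 0.2 SD, 5% random dropout and 150 replicates. On observed data it gave 0.595 at 3 months and 0.607 at 6 months, both above 0.58 by Monte Carlo noise. LOCF on the same datasets gave 0.566 and 0.577, about 5% lower in each case, as the formula predicts. The standard error at 3 months was 0.138 under LOCF against 0.144, because filled values count as observed. Only the 5% setting of this simulation completed.
- A separate simulation of the 3-month comparison (20,000 trials, 79 per arm, common gain 0.3 SD) gave LOCF estimates of 0.549, 0.520 and 0.485 at 5%, 10% and 16% missing. Coverage of the nominal 95% interval was 0.943, 0.929 and 0.901 with baseline correlation 0.5, and 0.942, 0.920 and 0.873 with correlation 0.7.

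**Step 5: patients missing only the 6-month visit.** LOCF carries the 3-month score. If a proportion d of each arm is missing in this way, the bias in the 6-month contrast is d × (3-month effect − 6-month effect). It is zero if the effect is stable. The documents give no trajectory from which to size it.

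**The case against.** The best defence is that the rule is conditional. LOCF applies only when missing values are few and random, and 16% is the whole planned dropout, which many would not call few. At 3–5% the contrast falls only to 0.563–0.551 and coverage at 5% is about 94%. With equal random dropout the 3-month bias is toward no difference, so it does not manufacture a superiority claim. The plan also promises results with and without imputation, so the observed-data analysis will be run and any discrepancy will be visible. All of this stands and limits the severity. It does not justify the rule. With no threshold for *few*, nothing stops LOCF being used at 10% or more. The natural reading of a rule that replaces missing data is that the filled dataset is the main one, although that is an inference. A side-by-side comparison exposes a bias but does not remove it.

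A reader might infer three stronger things that the documents do not support:

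- **LOCF will overstate durability at 6 months.** This needs an effect that fades after 3 months, and no such trajectory is given. For patients lost before 3 months the 6-month contrast is understated instead.
- **LOCF will create a spurious difference when dropout differs by arm.** The arithmetic is right: with an assumed 24% against 8% dropout and a common gain of 0.2 to 0.5 SD, the bias under no effect is 0.16 × 0.2 to 0.16 × 0.5, i.e. 0.03 to 0.08 SD against the arm with more dropout. But missingness that differs by arm is arguably not randomly allocated, and the plan then calls for multiple imputation. The gain and the dropout rates are also assumptions.
- **The plan is deficient for lacking a tipping-point analysis.** That is detail a protocol article may leave to the analysis plan.

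**Conclusion.** The concern holds in a limited form. In the few-and-random case the LOCF rule is unnecessary and biases the primary contrast, because the planned two-level model is already valid there on the observed visits. The relative attenuation equals the missing fraction: about 3–5% if few means 3–5%, and 16% at the planned dropout. At 16%, approximate power falls from 0.80 to 0.72, which gives back what the dropout allowance bought.

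The attenuation rests on random loss before 3 months at an equal rate in the arms and on the plan's effect of 0.58. The power figures also use the plan's two-group formula with unit SD, as an approximation to the mixed model. The coverage and standard-error figures depend on assumed correlations and gains.

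It would go too far to say that the trial's primary result is invalid. The rule is conditional, its effect is small at the low end, and the unfilled analysis is already planned alongside. Grade: should be fixed.

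**What to change.** 1. Delete the LOCF rule.
2. State that, when missingness is few and random, the primary analysis is the two-level model fitted to all observed data with no prior imputation.
3. Keep multiple imputation for the case where missingness is not random.
4. Keep the comparison of results with and without imputation, using multiple imputation in place of LOCF. Delta-shifted imputation would be a reasonable optional addition.

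The cost is a change of wording and a few lines of SAS or R code. No new data are needed and the sample size does not change. The article reports that recruitment is ongoing, so the change should be made and dated before any analysis.

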### The hypotheses

Primary hypothesis:
Cognitive training with computerised exercises is more effective than entertainment video gaming or the non-gaming control in improving patients’ working memory at a 3-month and/or 6-month follow-up.

Secondary hypotheses:
2.Cognitive training with computerised exercises is more effective than entertainment video gaming and the non-gaming control in improving patients’ cognitive and social functioning, experience of pleasure, and self-efficacy at a 3-month and/or 6-month follow-up.3.Cognitive training with computerised exercises is more effective than entertainment video gaming and the non-gaming control in improving negative symptoms in schizophrenia at a 3-month and/or 6-month follow-up.4.Cognitive training with computerised exercises is more effective than entertainment video gaming and the non-gaming control in improving neurocognitive outcomes (EEG signals, brain activity and structure) at a 3-month follow-up.

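### The trial is sized at a multiplicity-adjusted 0.01274 for four primary tests, but the analysis section declares P < 0.05 significant in all tests, so the stated rule does not hold the planned 5%

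*Protocol article*

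**What the plan says.** **Power analysis and sample size.** The article counts the primary tests: "Four pairwise interactions between the contrast of the two comparisons and the two time points will be tested". It then sets the level: "For multiple comparison tests of four, for a type I error level of 5% (two-sided), an adjusted significant level should be" 0.01274, which it carries through as "0.01274 /2 = 0.0064, and the corresponding z score for a one-tailed test should be 2.49". With an effect size of 0.58 and power of 0.8 it arrives at 66 per group, 198 in all. The same section says that the type I error is adjusted in the two-level model of the final analysis. Its list of comparisons also includes a third one: "cognitive training vs. non-gaming control group, and entertainment gaming vs. non-gaming control group".

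**The hypotheses.** The primary hypothesis is that cognitive training is "more effective than entertainment video gaming or the non-gaming control" at 3 and/or 6 months. The secondary hypotheses join the two comparators with *and*.

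**Data analysis, Cognitive and clinical outcomes.** The two-level model has group indicators G2 and G3, time indicators T2 and T3, and their interactions, which gives four interaction terms. No adjusted level, testing order or multiplicity procedure is attached to them. The section ends with the general rule: "In all tests, significant differences between groups will be detected with a 95% confidence level", and P values under 0.05 count as significant. No exception is made for the primary outcome.

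**The concern.** Two sections of one document give different significance levels for the same four tests. The sizing section uses 0.01274 and the analysis section uses 0.05. Allowing for repeated measures with a patient random effect does not adjust for testing four contrasts, so the model itself does not supply the promised adjustment.

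This affects the trial's main claim. A reader cannot tell whether P = 0.03 on the Letter-Number task, for one comparator at one time point, would be a primary success. Under the analysis section it would be; at the level used for sizing it would not. Because the hypothesis is disjunctive, such a result could be reported as confirming it even if CogniFit beat only treatment as usual. The Trial design section, however, presents the three arms as a test of superiority over both the active and the passive control.

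**Working it through.** **Inputs from the article:** overall two-sided error 5%; four tests; effect size 0.58; power 0.8; equal groups; 66 per group evaluable; analysis threshold 0.05.

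**Inputs not in the article:** the correlation between the 3-month and 6-month change estimates, called rho here. I vary it from 0 to 0.9. A random-intercept model with a shared baseline implies 0.5: each change has variance 2σ², and the two changes have covariance σ². The correlation between the two contrasts at one time point is 0.5, because they share the CogniFit arm and the groups are equal in size.

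**1. Reproduce the plan's own figures.**
- Sidak level for four tests: 1 − 0.95^(1/4) = 0.01274. Half of this is 0.0064, with z = 2.491.
- n per group = 2(z₁₋α/₂ + z₁₋β)² / ES² = 2(2.4909 + 0.8416)² / 0.58² = 66.03, or 65.99 with z rounded to 2.49. The stated 66 is confirmed.
- The exponent in the printed formula reads as 4, but the stated value 0.01274 is the one given by an exponent of 1/4. I treat this as a typesetting loss.

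**2. Error at the level stated in the analysis section (global null).**
- Independent tests: 1 − 0.95⁴ = 18.5%.
- Correlated tests were simulated: multivariate normal, 4 million draws per setting, contrast correlation 0.5. The table gives the chance that at least one of the four tests is significant.

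| rho | Two-sided, each at 0.05 | Favouring CogniFit only, each at 0.05 | Two-sided, each at 0.01274 |
|---|---|---|---|
| 0 | 17.3% | 8.9% | 4.8% |
| 0.5 | 16.1% | 8.1% | 4.5% |
| 0.7 | 14.9% | 7.4% | 4.2% |
| 0.8 | 13.9% | 7.0% | 3.9% |
| 0.9 | 12.6% | 6.3% | 3.5% |

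The two-sided columns compare with the planned 5%, and the favourable-direction column with half of that, 2.5%. With independent tests at 0.01274 the two-sided rate is 1 − (1 − 0.01274)⁴ = 5.0%.

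**3. What the mismatch means for sizing.** At 0.05 per test, 80% power needs 2(1.9600 + 0.8416)² / 0.58² = 46.7, so 47 per group. With 66 per group, power per test is 91.5% at 0.05 and 80.0% at 0.01274. The trial therefore already carries the patients that the stricter level requires.

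**The case against.** **Adjustment was intended.** The sizing section says so, and a separate analysis plan may give the procedure. The intent is on record, and an absent procedure alone would not be a finding. But the article does not leave the matter open: it states a rule for all tests that conflicts with its own sizing. Nor does it say that the P values are adjusted, and the paired 95% confidence level points to unadjusted ones.

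**The two-sided rate overstates false success.** This stands. A reader might infer that the primary hypothesis would be falsely confirmed about 14-16% of the time. The hypothesis is directional, and that figure also counts results in which CogniFit is significantly worse. The favourable-direction rate is about 7-8% at rho of 0.5 to 0.8. The 14-16% also belongs to that same assumed range of rho, which the article does not give.

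**The result depends on the word *or*.** This also stands. If CogniFit had to beat both comparators at the same time point, the favourable-direction rate at 0.05 would be about 0.8-0.9% under the global null (rho 0.5 to 0.8). If one comparator were certain to be beaten, it would be 3.9-4.5%. But the primary hypothesis says *or*, and the sizing section adjusts for four separate tests, which fits that reading.

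**The family might be six tests.** Because a third comparison is listed, a reader might infer six primary tests and an undersized trial. The documents do not support this. The sizing section counts four tests, and the model has four interaction terms. The third comparison only needs to be placed explicitly.

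**Conclusion.** The rule is wrong as written. The level that justifies 66 per group is not the level at which the analysis section says results will be judged, and at the stated 0.05 the planned 5% is not held. The conclusion rests on the disjunctive primary hypothesis, the global null and the shared-arm correlation of 0.5. The exact size also depends on the unstated between-time correlation, but every value examined is at least 2.5 times the planned rate (12.6% / 5% = 2.5 at rho 0.9), in the two-sided and the favourable-direction count alike. At 0.01274 per test the two-sided rate is 3.5-5.0%, so the article's own sizing level resolves the problem. The sample size itself is not in error.

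**What to change.** In the final paragraph of Cognitive and clinical outcomes, exempt the primary outcome from the 0.05 rule and state:

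- The primary family is the four CogniFit contrasts on the Letter-Number task: against entertainment gaming and against treatment as usual, at 3 and at 6 months.
- Each is tested at two-sided 0.01274, the level already used for sizing, with matching 98.7% confidence intervals. Holm-Sidak is an acceptable alternative because its first step is the same 0.01274. Plain Holm starts at 0.05/4 = 0.0125, so it is very slightly stricter at that step.
- Entertainment gaming against treatment as usual lies outside the primary family.
- Only the contrasts and time points actually rejected are claimed, so that a win over treatment as usual alone is not reported as superiority to entertainment gaming.

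The cost is a short paragraph and no extra patients. The article describes recruitment as ongoing; the change should be made before outcome data are examined by arm. The downside is that primary results with P between about 0.013 and 0.05 may no longer count as successes.
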